## Abstract

**Background:**

Most smoking efforts targeting young people have so far been focused on prevention of initiation, whereas smoking cessation interventions have largely been targeted towards adult populations. Thus, there is limited evidence for effective smoking cessation interventions in young people, even though many young people want to quit smoking. Mobile communication technology has the potential to reach large numbers of young people and recent text-based smoking cessation interventions using phones have shown promising results.

**Methods/design:**

The study aims to evaluate a newly developed text-based smoking cessation intervention for students in colleges and universities in Sweden. The design is a randomised controlled trial (RCT) with a delayed/waiting list intervention control condition. The trial will be performed simultaneously in all colleges and universities served by 25 student health care centres in Sweden. Outcomes will be evaluated after 4 months, with 2 cessation primary outcomes and 4 secondary outcomes. After outcome evaluation the control group will be given access to the intervention.

**Discussion:**

The study will examine the effectiveness of a stand-alone SMS text-based intervention. The intervention starts with a motivational phase in which the participants are given an opportunity to set a quit date within 4 weeks of randomisation. This first phase and the subsequent core intervention phase of 12 weeks are totally automated in order to easily integrate the intervention into the daily routines of student and other health care settings.

As well as providing data for the effectiveness of the intervention, the study will also provide data for methodological analyses addressing a number issues commonly challenging in Internet-based RCTs. For example, an extensive follow-up strategy will be used in order to evaluate the use of repeated attempts in the analysis, and in particular to explore the validity of a possible missing not at random assumption that the odds ratio between the primary outcome and response is the same at every attempt.

**Trial registration:**

ISRCTN: ISRCTN75766527, dated assigned 4 November 2014. Protocol version: Version 1, and date 7 November 2014.

**Electronic supplementary material:**

The online version of this article (doi:10.1186/s13063-015-0640-2) contains supplementary material, which is available to authorized users.

## Background

Worldwide, nearly 100.000 young people start smoking every day and in Sweden the annual number of new younger smokers is between 16,000 and 20,000 [1,2]. Longer-term reductions in the prevalence of smoking in the general population in Sweden have started to level off and in 2013 the proportions of daily smokers among both men and women were 11% [3]. In young people between 16 and 29 years of age the prevalence of daily smoking in 2013 was 12% among women and 7% among men, whereas occasional smoking was approximately twice as common in women and 3 times as common among men [3].

Smoking is responsible for more than 60 diseases and is globally the most important preventable cause of ill health and death. For every death related to smoking, more than 20 additional individuals will suffer from at least 1 serious smoking-related illness [4]. Tobacco is responsible for approximately 9.6% of the total disease burden in Sweden [5] and around 6,000 people die every year in Sweden due to smoking [1]. Many of the negative health effects of smoking develop after many years of smoking and there is a linear dose–response relationship between smoking and tobacco-induced diseases, such that the longer a person smokes the more likely the person will develop a smoking-related illness [1]. Most smokers start in their teens and over the course of a year most young smokers want to quit or cut down [6]. Among all smokers, around 65% in some studies want to quit and around half of all smokers make at least 1 quit attempt each year, but only 10% seek or gain access to evidence- based helping resources [7]. The addictive nature of smoking makes cessation difficult and the cost, time commitments and logistics associated with treatment are additional barriers [8].

Identifying effective interventions to help young people to quit smoking would have a major impact on population health. However, there is a limited amount of evidence for effective smoking cessation intervention in young people [2,9,10]. In a recent Cochrane review, 28 good quality studies were identified with about 6,000 young people included in various forms of tobacco cessation programmes. These include a variety of promising approaches, such as behavioural change support and motivational enhancement, but still the number of trials and participants are not large enough to judge which approaches are best implemented on a large scale [9]. Existing smoking cessation programmes also do not reach sufficient proportions of young smokers [9]. Thus, there is both a lack of knowledge on how best to reach young people and on how to effectively intervene with them, in order to reduce the number of young people still smoking [11].

During the last decade the development and dissemination of computerised health behaviour interventions have expanded exponentially, moving health behaviour change interventions from delivery in the health care sector into people’s homes and wherever they happen to be. An increasing number of Internet-based health behaviour change interventions show promising evidence of effectiveness in several life style areas [12-14].

In contrast to Internet-based interventions delivered on computers, mobile phone interventions have the capacity to interact in a more dynamic way with the individual with much greater frequency using short message service (SMS), more commonly known as text messages. Thus, mobile phone technology could provide a new mode of delivering personalised smoking cessation support. Since nearly all young people have a mobile phone and often use SMS to communicate with each other, SMS-based interventions could potentially be a vehicle for a large public health impact, even if only modestly effective [15-18].

At present, more than 50 smoking-cessation apps for smart phones are available to download. However, very few have evidence-based content [19]. Also, most apps need to be actively opened by the person. So, it is important not only to download the app but also to use it as intended [19]. This contrasts with SMS-based interventions where the person automatically receives a message with information or another intervention component and does not have to actively decide to continue accessing the intervention. This increases the potential for high levels of exposure and strong adherence to intervention content in real time in everyday settings.

Research on mobile phone-based interventions for smoking cessation has so far been very scarce. One of the first studies of a solely SMS-based intervention was performed in New Zealand in 2005 - the ‘Do u smoke after txt?’ study. The study showed a significant 6-week increased quit rate in the SMS group compared to the control group (28% versus 13%), whereas at 6 months the results were difficult to interpret due to missing values [18]. A later study, the ‘txt2Stop’ study from the UK, was based upon a modified version of the New Zealand intervention. Its pilot study showed at 6 months follow-up a self-reported quit rate of 26% in the intervention group compared with 12% in the control group [17], and in the main study the quit rate was 19.8% in the SMS intervention group compared to 13.5% in the control group. The biochemically verified abstinence rate was 10.7% in the SMS group and 4.9% in the control group [15].

In a recent Cochrane review only two additional studies besides the three studies above were identified; one of these also included the use of the Internet and other video messages sent via the mobile phone [20]. Since this review, five more randomised controlled trials (RCTs) have been published of solely SMS-based smoking cessation interventions [21-25]. Four of these showed promising results [21,22,24,25] although three were pilot studies not powered to detect significant differences between intervention and control group [22,24,25]. In the fifth study no significant differences were seen in short-term abstinence (assessed 8 weeks after randomisation) between a control group and participants receiving a 12-week SMS intervention. However, longer-term prolonged abstinence (assessed 6 months after randomisation) was significantly higher in the SMS group than in the control group (15.1% versus 8.9%) [23]. The central component of these interventions was daily text messages based upon various behaviour change theories and/or existing evidence-based guidelines for smoking cessation, during an intervention period of between 6 and 12 weeks.

In summary, although existing data are promising, proven effective smoking cessation interventions targeting young people are scarce and further research is needed to evaluate the effectiveness of innovative interventions capable of reaching young people [26,27]. Our aim is to present the study protocol of a RCT testing the effectiveness of a new SMS-based smoking cessation intervention for college and university students in Sweden.

## Methods/design

### Design

This is a 2-arm RCT study in which participants are randomised to an intervention (group 1) or a waiting list (group 2). In Additional file 1, the recommended items included in the reporting of the RCT are listed. After the 12-week intervention all participants in both groups will be asked to complete a follow-up questionnaire after which the control group will be given access to the intervention. The study will be performed simultaneously at all universities and colleges in Sweden.

### Objectives and hypotheses

The objective of the study is to evaluate the effectiveness of a SMS-based smoking cessation intervention. Participants in both the intervention and control group are told that they are free to seek any other treatment they want during the trial in the same manner as in previous studies [15-18].

Six hypotheses in total are being tested. The 2 primary hypotheses are that a greater proportion of participants in the intervention group than in the control group will report: 1) prolonged abstinence (8 weeks) and 2) recent abstinence (4 weeks) at follow-up. Secondary hypotheses are that the intervention group compared with the control group will report: 3) greater proportions of current abstinence (1 week); 4) a higher number of quit attempts; 5) greater use of other smoking cessation services; and 6) smoking fewer cigarettes among those still smoking at follow-up.

### Participants, setting and recruitment

All 25 student health care centres responsible for preventive services for students in Sweden will participate in recruiting interested smokers during a 4-week period in October 2014, through advertisement at strategic places in each college and university. This includes leaflets, posters and information on the local website and in some cases the official Facebook account. Participants register their interest in taking part in the study by sending a SMS to a dedicated telephone number. Interested students will receive mail with more information about the study and how to participate. Also, 19 student health care centres will send an invitation by Email to all students at the end of October 2014 with 2 reminders with 1 week apart, allowing the participants to respond up to 7 days after the last reminder. This means that recruitment of participants will be finalised at the end of the second week of November 2014. A flowchart of the study recruitment procedure is given in Figure 1. Eligible participants are students who are daily or weekly smokers and willing to set a quit date for smoking cessation within the next 4-week period. Exclusion criteria are non-smokers/occasional smokers not smoking every week, and smokers not willing to set a quit date within 4 weeks.

**Figure 1 Fig1:**
[figure not shown]
**Consolidated Standards of Reporting Trials (CONSORT) flow chart.** CONSORT flow chart illustrating all steps in the study from enrolment to allocation and follows up. Inclusion and exclusion criteria are also specified as well as outcome measures.

### Randomisation and other study procedures

Smokers who respond to the invitation Email and want more information about the study will be referred to a page with more information about the study emphasising that only students who are daily or weekly smokers willing to set a stop date within a month are eligible for the study. Most previous SMS-based smoking cessation studies have used the inclusion criteria - willing to set a stop date with 2 to 4 weeks - facilitating recruitment of a more engaged population both in the intervention and control group and thereby avoiding a larger drop-out of randomised participants before the specified quit date [15,18,23].

By emphasising that participants should be willing to set a stop date this would prevent randomised participants dropping out of the study before completing the intervention. After having read the information about the study all participants gave informed consent to participate by clicking on a link. After informed consent was obtained the participants were guided to a baseline assessment page. The hyperlink contained within the body of the Email is no longer valid after completion of the questionnaire when the responses are stored in the study database. This prevents multiple responses, while allowing the questionnaire to be completed in more than one session if required. After completion of the baseline assessment the students will be asked to provide their telephone number. Then they will immediately receive a SMS that will have to be responded to by writing, ‘start’, in order to confirm that they had stated the right telephone number.

Participants will immediately be randomised to an intervention or waiting list (control) group. Each participant is allocated a number 1 or 2 with equal probabilities using Java’s built in random number generator (java.util.Random). Randomisation is thus fully computerised, does not employ any strata or blocks, and is not possible to subvert, as this and all subsequent study processes are fully automated.

After randomisation, group 1 will start the intervention immediately with a motivational phase between 1 to 4 weeks, designed to encourage the participants to set a quit date. The participants are given an opportunity to set a quit date every week during this 1 to 4-week motivational phase. If no active quit date is set within this 4-week period, the participant defaults to their originally provided commitment and is given a quit date immediately after the 4-week motivational phase is completed. This procedure is in accordance with the inclusion criteria and informed consent. After setting a quit date the core intervention programme runs for 12 weeks.

Participants in the control group will receive a SMS informing them that they have been allocated to the control group and that they will receive access to the intervention after 4 months. In addition both groups will receive a SMS every fortnight thanking them for participating in the study. Towards the end of the 4-month period both groups are informed that they will receive the follow-up questionnaire in 2 weeks time.

### Blinding

Both groups will be aware that they are participating in a research study and that they will be randomised to an intervention or control group after having confirmed their telephone number. After the 4-month follow-up, the waiting list group will receive access to the intervention. As all study procedures are automated, the research team will have no direct contact with the study participants and so there is no possibility to bias the data collection. The study was approved by the Regional Ethical Committee in Linköping, Sweden (Dnr 2014/217-31).

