### Outcome evaluation

The baseline questionnaire contains 19 questions about sociodemographic data and smoking habits. The participants will be asked to state their age, gender, marital status and years of smoking and, if using Swedish snuff (‘*snus*’), how much per day. Then follows the 6 questions of Fagerström’s Nicotine Dependence Scale and a question on how important it is for the participants to quit smoking with response option on a scale from 1 to 10, where 1 stands for not important at all and 10 very important. All participants will be asked if they ever have tried to stop smoking before (and if so how many times); if they ever have tried nicotine replacement (if so how many times); if they have been prescribed drugs for smoking cessation, and if they have received professional counselling or if they have called the national quit smoking help-line.

After 4 months, a link to an electronic follow-up questionnaire will be Emailed to all participants. Initially, 2 reminders 1 week apart will be sent to non-responders. In order to minimise attrition those participants still not responding will receive additional Email reminders every second day for 6 days (that is 3 Emails). If still not responding, the non-responders will receive a SMS every second day for 6 days (that is 3 SMS) with only 2 questions to answer, to capture the 2 primary outcome measures. Lastly, those still not responding will be phoned with a maximum of 10 calls per participant. Also, in the invitation to answer the follow-up questionnaire the participants will be told that they are offered the opportunity to be part of a draw for a number of iPads (Apple Inc., Cupertino, CA, USA) after having answered the follow-up questionnaire.

Outcome measures are as follows:

*Primary outcome measures*:Self-reported prolonged abstinence (defined as having not smoked more than 5 cigarettes in the last 8 weeks).Self-reported 4-week point prevalence of smoking abstinence (not having smoked a single cigarette).

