#### Sensitivity analyses

Sensitivity analysis will explore the effects of departures from the missing at random assumption in the main analysis [37-40]. As suggested by Jackson *et al*. [39], we will quantify departures from the missing at random (MAR) assumption by the informatively missing odds ratio (IMOR). We will assume that the IMOR is the same in each randomised group and we will vary the IMOR over the range 0.5 to 1; if 10% of observed data are abstinent then this range implies that from 5% to 10% of missing data are abstinent. We will also allow the IMOR to be 0 (missing = smoking, the Russell standard) [41]. Further, we will use data on the number of follow-up Emails, texts and phone calls needed before an individual responded to explore the plausibility of the MAR assumption: first by exploring the association between quitting and number of follow-up attempts needed, and then by fitting the repeated attempts model of Jackson *et al*. [38,39] which will allow us to both estimate the degree of departure from MAR and to adjust for departure from MAR.

In associated methodological work, we will also use the data on the number of follow-up Emails, texts and phone calls needed before an individual responded to explore: 1) the implications of a less intensive data collection regime, and 2) the validity of the assumptions of the repeated attempts model, including that data collected at later attempts are of equal quality.

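### The Blinding section rules out bias in data collection because everything is automated, but remaining non-responders are phoned for their outcomes and that step is not covered

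*Protocol article*

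**What the plan says.** Two sections of the protocol article rest on automation. Randomisation and other study procedures, after describing computerised allocation, adds that "this and all subsequent study processes are fully automated". The Blinding section goes further. It takes automation to be complete and concludes that "the research team will have no direct contact with the study participants and so there is no possibility to bias the data collection".

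The Outcome evaluation section sets out follow-up in steps: an emailed link with two reminders, three more Emails, then three SMS "with only 2 questions to answer, to capture the 2 primary outcome measures". The final step is different in kind: "Lastly, those still not responding will be phoned with a maximum of 10 calls per participant".

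The Data analysis section includes everyone with follow-up data, and Primary analyses uses complete cases. The Sensitivity analyses section uses the "number of follow-up Emails, texts and phone calls needed before an individual responded", so an answer given by phone counts as a response. The Discussion accepts that abstinence is self-reported and unverified.

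**The concern.** The Blinding section and the telephone step cannot both be right as written. On the ordinary reading of a phone call, a person asks about smoking and records the answer. That is contact, and it is not automated.

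The outcome is open to influence. It is a self-report without verification, and control participants have been told their allocation. If a caller knew the arm, prompting, persistence below the call limit, or the coding of an ambiguous answer could differ between groups. The Discussion assumes that over-reporting is equal in the two groups, and differential handling of calls would break that assumption.

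The phone answers are used twice. They count in the primary comparison. They are also the last attempts in the repeated-attempts model, which is meant to measure departure from missing at random. An effect of the caller on late answers could be read by that model as a difference between early and late responders.

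**Working it through.** **Step 1: the statements side by side.**
- Blinding: all procedures automated, no direct contact, therefore no bias in data collection.
- Randomisation and other study procedures: everything after randomisation automated.
- Outcome evaluation: up to 10 phone calls to each remaining non-responder. The article does not say that these calls are automated.
- Data analysis, Primary analyses and Sensitivity analyses: answers obtained this way are analysed.

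The first two statements fail once the third is true, and nothing elsewhere in the article reconciles them. The article also lists, among the assumptions of the repeated-attempts model still to be examined, "including that data collected at later attempts are of equal quality". Treating that as open does not fit with declaring bias impossible.

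**Step 2: the plan's own figure, used below as the denominator.** Inputs from Sample size: 10% against 5%, 80% power, two-sided 0.05, continuity correction.
- Without correction: n₀ = [1.96√(2 × 0.075 × 0.925) + 0.8416√(0.10 × 0.90 + 0.05 × 0.95)]² / 0.05² = 434.4, so 435.
- With correction: n = (434.4/4) × [1 + √(1 + 4/(434.4 × 0.05))]² = 473.6, so 474 per group, as stated.

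**Step 3: how large could a caller effect be?** The article gives neither the share reached by phone nor any caller error rate, so both are assumptions. Suppose there is no true effect, 5% are abstinent in both arms and 474 are analysed per arm. Let f be the share of answers taken by phone. Let m be the share of phoned intervention-arm smokers wrongly recorded as abstinent.

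Spurious difference: d = f × m × 0.95.

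False-positive rate of a two-sided 5% z test (no continuity correction): Φ((d − 1.96·se₀)/se₁) + Φ((−d − 1.96·se₀)/se₁), where se₀ is the pooled and se₁ the unpooled standard error.

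| f | m | d (points) | d as share of 5 points | False-positive rate |
|---|---|---|---|---|
| 5% | 2% | 0.095 | 1.9% | 5.1% |
| 10% | 5% | 0.475 | 9.5% | 6.2% |
| 10% | 10% | 0.95 | 19% | 9.9% |
| 20% | 10% | 1.90 | 38% | 23.5% |
| 30% | 10% | 2.85 | 57% | 43.2% |

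Worked row (f = 10%, m = 10%): d = 0.10 × 0.10 × 0.95 = 0.0095, se₀ ≈ se₁ ≈ 0.01478, and the rate is Φ(−1.317) + Φ(−2.603) ≈ 0.094 + 0.005 ≈ 0.099.

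The range runs from negligible to material. It shows sensitivity to two unknowns and is not an estimate for this trial.

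**The case against.** The case on the other side has five parts.

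- **Caller knowledge.** A reader might infer that callers know the arm, or that the plan has no safeguard. The article does not support either. It does not name the callers, and masked or outside callers are compatible with its text. Call procedures are also something a journal article commonly leaves to the full protocol. This stands. It does not rescue the Blinding section, which makes an absolute claim and gives automation as the only reason.
- **Randomisation.** A reader might infer that the calls undermine allocation. They do not. Allocation is complete about four months before any call, and the claim that it cannot be subverted is unaffected. Only the extension to all later processes is wrong.
- **Call limit.** The cap of 10 is already set per participant without regard to arm, so no equal-limit rule is needed. The number of calls made below the cap could still vary.
- **Planned work on late data.** The article will explore the link between quitting and number of attempts, a less intensive collection regime, and the quality of late answers. This overlaps in part with an analysis that leaves out phone answers. However, the last two are associated methodological work, and none of it deals with caller masking or compares the trial result by mode of collection.
- **Phone content.** The two-question format is attached to the SMS step, and the article does not say what is asked by phone. This is correct, and it is a reason to fix the script.

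**Conclusion.** The contradiction is certain, because it rests on the article's own sentences. The plan claims a property, bias-free data collection through automation, that its last follow-up step does not have. The outcomes exposed are the unverified, self-reported answers of participants reached by phone, and these enter both the primary analysis and the repeated-attempts model.

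The size of any bias is not established. It depends on the share reached by phone and on how callers behave, and the documents give neither. A reader might take a figure from the table as the expected distortion. The documents support only the range, and its lower end is harmless. Nothing here shows that bias will occur. The stated reason for excluding it does not apply to the calls, and the remedy is cheap enough that the point should be acted on.

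**What to change.** 1. Withdraw the statement in Blinding that data collection cannot be biased. In Blinding and in Randomisation and other study procedures, limit the automation claims to randomisation, intervention delivery and data collection by Email and SMS.
2. State who makes the calls. Give them a list without allocation and a fixed script that asks the two primary outcome questions before anything that could reveal the arm.
3. Add a sensitivity analysis of both primary outcomes that excludes phone-collected answers. The attempts are already to be counted by type, so the mode of collection should be available.

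The cost is a short script, one column removed from the call list, corrected wording and one extra analysis. That analysis has fewer participants. A change in its result could reflect real differences in people who respond late as well as a caller effect, so it should be read as a check and not as a correction. The calls follow the 4-month assessment and recruitment was still open at submission, so on the article's timetable all of this could be in place before the first call.
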